**Fig. 2 Fig2:**
[figure not shown]
Evaluation flow chart. AF, atrial fibrillation; OAC, oral anticoagulant; NOACs, non-vitamin K antagonist oral anticoagulants; VKA, vitamin K antagonist oral anticoagulant; TTR, the percentage of time in the target INR range

**Table 2 Tab2:** The dose-adjustment criteria for the NOACs according to the Chinese labeling

Drugs	Dabigatran	Rivaroxaban	Edoxaban
Standard dosing	150 mg bid	20 mg qd	60 mg qd
Age ≥ 75 years	110 mg bid	15 mg qd	Not mentioned
Weight < 60 kg	Not mentioned	15 mg qd	30 mg qd
Renal impairment dosing	CrCl 30 ~ 50 ml/min: 150 mg bid/110 mg bid (high risk of bleeding); CrCl < 30 ml/min: avoid; dialysis: avoid	CrCl 15 ~ 50 ml/min: 15 mg qd; CrCl < 15 ml/min: avoid; dialysis: avoid	CrCl: 15 ~ 50 ml/min: 30 mg qd; dialysis: avoid
Hepatic impairment	Child–Pugh C: avoid	Child–Pugh B: avoid; Child–Pugh C: avoid	Child–Pugh C: avoid
Drug-drug interaction	110 mg bid: verapamil: avoid with cyclosporin, ketoconazole, itraconazole, dronedarone	Not recommend: fluconazole, itraconazole, ketoconazole, voriconazole, HIV protease inhibitors	30 mg qd: cyclosporin, dronedarone, erythromycin, ketoconazole

*CrCl* creatinine clearance

### Data collection and management

All pertinent information of clinical patients in the group will be documented after enrollment, which includes demographic details, diagnosis, drug usage, test outcomes, and follow-up results. All data will be collected in accordance with standard procedures outlined in Table 3. It is important to note that this trial does not involve collecting biological specimens for storage. The medical information of each patient enlisted in the SDM tool, which is a WeChat mini-program-based model, will be saved in a monitoring database. Professionals will ensure that patients’ personal information is secure and that all files remain confidential. If there are any bugs or data leakage, all people will stop using the SDM until the problem is solved and the ethics committee approves resumption. The users can contact the researchers at any time if they encounter any difficulties, and a response will be given within 24 h. For severe adverse events, researchers will report them to the ethics committee within 24 h. If it is attributed to the SDM tool, the ethics committee and the PI can terminate prematurely and conduct interim analyses. The final trial dataset will be made available to the PIs, research team members, and authorized personnel who are directly involved in the study. These individuals will be granted access to the dataset for the purpose of data analysis, interpretation, and publication of the trial results. Researchers or organizations interested in obtaining specific data related to our trial can make a formal request, and we will strive to provide the requested information promptly while adhering to any applicable data protection laws and regulations. Access to the SDM tool intervention and its corresponding code can be made available upon request to the PI or corresponding author of this study. However, restrictions may apply to protect intellectual property or preserve confidentiality. These limitations will be disclosed transparently during the access request process.

**Table 3 Tab3:** Schedule of study activities

Time points	Day of admission (D0)	Follow-up (months)					
		1	3	6	12	18	24
**Enrollment**							
Informed consent	×						
Inclusion/exclusion criteria	×						
Demographics^a^	×						
Past medical history^b^	×						
Comedications^c^	×	×	×	×	×	×	×
**Assessment**							
Liver function^d^	×	×	×	×	×	×	×
Kidney function^e^	×	×	×	×	×	×	×
Heart function^f^	×	×	×	×	×	×	×
Stroke risk^g^	×	×	×	×	×	×	×
Bleeding risk^h^	×	×	×	×	×	×	×
Coagulation function	×	×	×	×	×	×	×
Patient-reported outcomes							
AKT^i^	×	×	×	×	×	×	×
MARS-5^j^	×	×	×	×	×	×	×
ACTS^k^	×	×	×	×	×	×	×

^a^Age, height, weight, gender, ethnicity, date of birth, history of smoking, and alcohol

^b^Hypertension, coronary heart disease, diabetes, and history of stroke

^c^Antiplatelet agent and interacting combination medications with NOACs, such as antiarrhythmic therapy, itraconazole, ketoconazole, and ritonavir, etc

^d^Child-Pugh score

^e^CrCl, calculated using Cockroft-Gault formula

^f^LVEF%

^g^CHA2DS2-VASc score is a rating of risk for stroke in patients with AF, items of 1 point each for congestive heart failure, hypertension, diabetes mellitus, vascular disease, age 65–74 years, and sex category [female] and 2 points each for a history of a stroke, TIA, or age ≥ 75 years

^h^HASBLED score is a rating of risk for bleeding in patients with AF, 1 point each for hypertension, abnormal renal/liver function, stroke, bleeding history or predisposition, labile INR, 65 years or older, drugs/alcohol concomitantly

^i^Anticoagulation Knowledge Tool

^j^Medication Adherence Reporting Scale

^k^Anti-Clot Treatment Scale

### Sample size

This multicenter, cluster-randomized clinical trial aims to evaluate the occurrence of bleeding events as the primary outcome. The anticoagulation bleeding rate of patients with AF in our hospital was previously found to be 20% [24], and an effective intervention reduces the incidence of bleeding by 15% [35]. We set the power at 80% with a bilateral two-tailed significance of 5%. To achieve a sample size of 88 cases in both the intervention and control groups, with a 20% loss to follow-up rate, we estimated a minimum of 110 cases in each group. However, taking the clustering into account, we increased the sample size to account for the design effect to achieve the required statistical power under cluster randomization. Therefore, using the bleeding rate as the calculating target and a design effect of 2, we estimated a sample size of 440, which was calculated using the PASS software version 15.

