**Methods:**

The study will be a prospective, cluster randomized controlled trial involving 440 patients with AF in 8 community health service centers (clusters) in Shanghai, China. The SDM group will receive anticoagulation management through the novel SDM tool, while the control group will receive standard care. The follow-up period will be at least 2 years. The primary outcome will be any bleeding event, while secondary outcomes include the accordance of stroke prophylaxis for AF according to the current guidelines, time in therapeutic range (TTR), the occurrences of major bleeding and thrombosis events, and patient knowledge, adherence, and satisfaction.

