### Strengths and limitations

This study has significant advantages, as it is a large-scale multicenter cluster randomized controlled trial involving a substantial number of participants. However, there are some limitations to this research. Firstly, the 24-month period may not be long enough to assess the effect on clinical outcomes such as thromboembolic events. Therefore, future studies should consider longer follow-up periods to evaluate the effects of the intervention over an extended period. Secondly, it is possible that those who agreed to participate in the research might be more interested in their own health, leading to a higher adherence to medication therapy than the general population with AF. This could potentially affect the generalizability of the study findings.

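### Doubling the sample for a design effect of 2 does not secure 80% power with four centres per arm: on 6 degrees of freedom it is about 73–78%

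*Protocol article*

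**What the plan says.** The calculation is in the Sample size section of the protocol article. Its inputs are:

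- Control rate: "The anticoagulation bleeding rate of patients with AF in our hospital was previously found to be 20" per cent.
- Effect: "an effective intervention reduces the incidence of bleeding by 15" per cent.
- Error rates: "We set the power at 80% with a bilateral two-tailed significance of 5" per cent.
- Base size: "To achieve a sample size of 88 cases in both the intervention and control groups", raised to 110 per arm for 20% loss to follow-up.
- Clustering: a design effect of 2, giving 440. The reason given is "taking the clustering into account, we increased the sample size to account for the design effect to achieve the required statistical power".

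The Abstract fixes the number of randomised units: "440 patients with AF in 8 community health service centers (clusters". Randomization and blinding gives 1:1 allocation, so four centres per arm. No ICC, and no cluster size to which the design effect of 2 applies, is stated. Statistical analyses names chi-square or Fisher's exact tests for categorical outcomes. Strengths and limitations says "it is a large-scale multicenter cluster randomized controlled trial" and does not mention the small number of randomised units.

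**The concern.** The design-effect method corrects one consequence of randomising centres: outcomes within a centre are correlated, so each patient carries less information. It leaves out a second. The between-centre variation has to be estimated from the centres themselves, and with four per arm that leaves 2 × (4 − 1) = 6 degrees of freedom. The reference distribution is then t with 6 degrees of freedom, not the normal.

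The section goes beyond describing an inflation factor. It says the inflation achieves the required power. That can be tested with the plan's own figures. If it fails, the trial is presented with a property it does not have, and a null result could be read as firmer evidence of no effect than eight centres can give.

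**Working it through.** **1. Reproduce the plan's figures.** Read the 15% as percentage points, so 20% versus 5%. A relative reduction of 15% (20% versus 17%) would need 2,629 per arm, so only the absolute reading fits. For two proportions, two-sided 5%, 80% power, with p̄ = 0.125:

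- Without continuity correction: n = [1.960·√(2·0.125·0.875) + 0.842·√(0.20·0.80 + 0.05·0.95)]² / 0.15² = 75.1, so 76.
- With continuity correction: (75.1/4)·[1 + √(1 + 4/(75.1·0.15))]² = 87.9, so 88.
- Loss: 88/0.8 = 110 per arm.
- Clustering: 110 × 2 arms × 2 = 440.

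All three stated figures (88, 110, 440) reproduce.

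**2. Information left after the planned loss.** 440 × 0.8 = 352 analysed, which is 176 per arm and 44 per centre. Enrolled per centre: 440/8 = 55. From design effect = 1 + (m − 1)·ICC = 2, the implied ICC is:

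- 1/43 = 0.0233 if m = 44 analysed;
- 1/54 = 0.0185 if m = 55 enrolled.

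**3. Power if the design effect of 2 holds at 44 analysed.** Effective n per arm = 176/2 = 88.

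- SE = √[(0.160 + 0.0475)/88] = 0.0486
- Noncentrality = 0.15/0.0486 = 3.09
- Normal critical value 1.960: power 87%
- t on 6 degrees of freedom, critical value 2.447: power **73.1%** (70.9% with a pooled SE)

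**4. Power if the design effect of 2 holds at 55 enrolled.** With 44 analysed the design effect is 1 + 43 × 0.0185 = 1.80, and effective n = 176/1.80 = 98.0 per arm.

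- SE = √(0.2075/98.0) = 0.0460
- Noncentrality = 3.26
- t on 6 degrees of freedom: power **77.5%**

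**5. Check by simulation.** Beta-binomial outcomes, a t-test on the eight centre proportions, 100,000 replicates: 74.2% power at ICC 0.0233 and 78.7% at ICC 0.0185. With no true difference this test rejects in 4.9% and 5.1% of replicates (20% bleeding in both arms), so it holds its level.

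**6. Sensitivity to the ICC** (44 analysed per centre, 6 degrees of freedom, unpooled SE):

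| ICC | Design effect | Effective n per arm | Power |
|---|---|---|---|
| 0.01 | 1.43 | 123.1 | 86% |
| 0.016 | 1.69 | 104.3 | 80% |
| 0.0185 | 1.80 | 98.0 | 77% |
| 0.023 | 2.00 | 88.0 | 73% |
| 0.05 | 3.15 | 55.9 | 54% |

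Reaching 80% on 6 degrees of freedom needs a noncentrality of 3.37, against 2.80 with a normal critical value.

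**The case against.** **The ICC is not stated, so no single power figure follows.** This stands. The article multiplies enrolled numbers, so tying the design effect to 55 per centre is at least as natural as tying it to 44. A reader might infer that power is simply 73%. The documents support a range of about 73–78%, and the shortfall may be as small as two points.

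**Power reaches 80% at a lower ICC or with less loss.** The arithmetic is right: about 80% at ICC 0.016, and 82% with no loss (110 effective per arm). Multiple imputation and repeated visits may also recover some information from patients lost late. But the first case departs from the plan's design effect of 2 and the second from its 20% loss. Neither rescues the claim on the stated inputs.

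**The planned chi-square or Fisher test would show more power.** It would, but only by ignoring the clustering that the sample size assumes. With no true difference, simulation of the unadjusted chi-square test gives a type I error of about 16% at ICC 0.0233 and 14% at 0.0185. Power from such a test cannot support the claim. It does follow that a restated power must name the analysis it belongs to.

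**The arithmetic is sound.** It is. A reader might infer a calculation error, but 88, 110 and 440 all reproduce. The continuity correction even adds a margin that partly offsets the penalty and is already counted in the 73%. The fault lies in the method and in the claim attached to it.

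**The large-scale description.** A reader might call this an error too. It is a choice of adjective. The substantive gap is that the eight randomised units are not listed as a limitation.

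**Conclusion.** The concern holds as a statement about the claimed power. On the plan's own 20% versus 5%, 20% loss and design effect of 2, a valid analysis of four centres per arm has about 73% power (71–74% across the variance formula and simulation) if the design effect refers to patients analysed. It has about 77–79% if it refers to patients enrolled. Both are below the 80% that the section says is achieved.

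The result assumes equal centre sizes, which the article does not guarantee; unequal sizes would lower power further. It also assumes the absolute reading of the 15% reduction.

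A reader might go further and conclude that the trial is badly underpowered, pointing to 54% at ICC 0.05. That ICC is hypothetical: nothing in the article supports it over a smaller one, and at 0.01 power would be 86%. What is established is a shortfall of roughly 2 to 7 points, and a strong dependence on an ICC that is not stated.

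**What to change.** Keep 440 patients and eight centres. In the Sample size section:

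- replace the claim of achieved power with about 73–78% for 20% versus 5%, with eight centres, 6 degrees of freedom, a design effect of 2 and 20% loss;
- say that this refers to a cluster-level analysis, or a model with a small-sample correction, and make Statistical analyses agree, since it now names only chi-square or Fisher tests for this outcome;
- state the ICC and the cluster size behind the design effect of 2. Once these are fixed, the range becomes one figure;
- give power over a range of ICCs, for example 0.01: 86%; 0.016: 80%; 0.023: 73%; 0.05: 54%.

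In Strengths and limitations, list the eight randomised units as a limitation.

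The cost is a few rewritten sentences and one short table. No patients, centres or visits are added, so the change is still possible although enrolment began in October 2022.

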### Statistical analyses

In accordance with standard practice, continuous variables will be presented as means ± standard deviation, while categorical variables will be expressed as proportions. The Kolmogorov–Smirnov test will be utilized to determine the normality of the data. Student’s *t*-test or Mann–Whitney’s *U*-test will be applied to compare two groups, depending on the distribution of the data. For categorical data, comparisons between the groups will be performed using the chi-square or Fisher’s exact tests. Time in therapeutic range (TTR) will be evaluated for patients on warfarin. Multiple imputations will be used to fill in missing values, and both per-protocol (PP) analysis and intention-to-treat (ITT) analysis will be conducted. Subgroup analyses will be performed based on patients’ age groups, treating hospitals, liver or kidney function, the type of anticoagulants used, etc. Statistical significance will be assumed for *p* values less than 0.05. All statistical analyses will be conducted with the IBM SPSS version 22.0 software.

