
## Methods

### Study design

This study will be a cluster randomized controlled trial conducted from October 2022 to April 2024 in eight community health service centers in Shanghai, China. The trial will compare the efficacy of using the shared decision-making (SDM) tool, I-Anticoagulation, versus the usual care in treating patients with AF. The clusters will be randomly assigned to either the SDM or control group, as depicted in Fig. 1. Consecutive patients with AF will be enrolled in the study, with those in the SDM group being treated using the I-Anticoagulation tool, while those in the control group receiving standard care. The study was registered on July 23, 2022, in the Chinese Clinical Trial Registry, with the registration number ChiCTR2200062123. This protocol was designed and described according to the standard protocol item—Recommendations for Interventional Trials–Artificial Intelligence (SPIRIT-AI) extension published in 2019 [25] (see Additional file 1).

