### Randomization and blinding

To avoid any risk of contamination between the SDM and control groups, cluster randomization will be implemented in this trial. The intervention provided to patients with AF will be grouped by clinicians in a single community health service center. Computer-generated randomization will be used to allocate the intervention and control groups in a 1:1 ratio following AF confirmation. The allocation results of each community health center will be told to the administrators by telephone. Each administrator only knows the result of his or her own site. The researchers, participants, and data analysts will not be blinded, but the participants will not be allowed to know the outcomes of this study.

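### The named tests ignore the eight randomised centres, so the nominal 5% error rate is about 17% for the chi-square test under the trial's own design effect of 2

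*Protocol article*

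**What the plan says.** The design is clustered throughout the protocol article. The abstract describes a "cluster randomized controlled trial involving 440 patients with AF in 8 community health service centers (clusters"). The Study design section says "The clusters will be randomly assigned to either the SDM or control group". The Randomization and blinding section repeats that "cluster randomization will be implemented in this trial" and gives a 1:1 ratio, which means four centres per arm.

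The Sample size section acts on this. It arrives at 88 per group, raises that to 110 for 20% loss, and then says "we increased the sample size to account for the design effect to achieve the required statistical power under cluster randomization". A design effect of 2 brings the total to 440.

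The Statistical analyses section does not carry this through. On yes/no and other categorical outcomes it says "comparisons between the groups will be performed using the chi-square or", with the exact test of Fisher as the alternative. Continuous outcomes get a t-test or a Mann-Whitney test, one of which "will be applied to compare two groups, depending on the distribution of the data". The threshold is p < 0.05. Centre enters only as one of several subgroup factors, under the label of treating hospitals. The primary outcome, any bleeding, is a yes/no event and so falls under the chi-square or Fisher test.

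**The concern.** The sample size assumes that patients in one centre resemble each other enough to double the variance of the arm comparison. The tests then assume that they do not resemble each other at all. Both cannot be right.

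If the design effect is 2, the unadjusted standard error is too small by a factor of √2 ≈ 1.41. Confidence intervals are too narrow by the same factor, and p-values are too small. A tool with no effect would be declared beneficial or harmful far more often than the stated 5%. Doubling the number of patients does not repair this. More patients in the same eight centres reduce random error, but they do not make a standard error computed as if patients were independent correct.

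The same direction of error applies to the arm comparisons of the secondary outcomes. The article says that its findings may inform guidelines and policy, so the false-positive rate matters.

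**Working it through.** **Inputs from the article.** Eight centres, 1:1, so four per arm; 440 patients, so 440/8 = 55 per centre; 20% loss, so 0.8 × 55 = 44 per centre; two-sided 5% and 80% power; control bleeding rate 20%; a reduction of 15%; design effect (DE) 2. No intracluster correlation (ICC) is given.

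**Reproducing the plan's figure.** Reading the reduction as absolute (20% against 5%), with d = 0.15 and mean proportion 0.125:

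- Without continuity correction: n = [1.96 × √(2 × 0.125 × 0.875) + 0.842 × √(0.20 × 0.80 + 0.05 × 0.95)]² / 0.15² = 75.1, so 76 per arm.
- With continuity correction: n = (75.1/4) × [1 + √(1 + 4/(75.1 × 0.15))]² = 88 per arm.
- Loss: 88/0.8 = 110. Design effect: 110 × 2 arms × 2 = 440.

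The stated 88, 110 and 440 come out exactly, so the design effect of 2 is what doubled the trial.

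**Implied ICC.** From DE = 1 + (m − 1) × ICC, a DE of 2 means ICC = 1/54 = 0.0185 at m = 55, or 1/43 = 0.0233 at m = 44.

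**Error of the unadjusted test.** If the true variance is DE times the one the test uses, the test rejects under the null with probability 2 × (1 − Φ(1.96/√DE)). At DE = 2 this is 2 × (1 − Φ(1.386)) = 16.6%.

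| Assumed DE | Two-sided error at nominal 5% |
|---|---|
| 1.2 | 7.4% |
| 1.5 | 11.0% |
| 1.8 (ICC 0.0185, 44 per centre) | 14.4% |
| 2 (the article's value) | 16.6% |
| 3 | 25.8% |

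**Check by simulation.** Beta-binomial data were generated under no effect, with four centres per arm, DE = 2, bleeding rates from 10% to 20%, and 40,000 replicates per setting.

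| Test | Rejection rate |
|---|---|
| Pearson chi-square | 16% to 17% |
| Continuity-corrected chi-square (close to Fisher) | 13% to 14% |
| t-test on the eight centre proportions, 6 df | about 5% |

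At 44 per centre, the Pearson test rejects in about 10% of null trials at an ICC of 0.01 and about 27% at 0.05. For a continuous score, a patient-level t-test rejects in about 16% at an ICC of 0.023 and 25% to 28% at 0.05. These other ICCs are assumptions chosen to show the range.

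**Power of the valid test.** For the 6-df centre-level t-test with 20% against 5% and DE = 2, the standard error is √(2 × 0.2075/n), where n is the number analysed per arm and 0.2075 = 0.20 × 0.80 + 0.05 × 0.95. The critical value is 2.447.

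- n = 176 (44 per centre): noncentrality 0.15/0.0486 = 3.09, power about 73% (74% to 75% by simulation).
- n = 220 (55 per centre): noncentrality 0.15/0.0434 = 3.45, power about 82% (83% by simulation).

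**The case against.** The strongest reply is that the article condenses protocol version 3.0 and that a fuller analysis plan may exist. Its Statistical analyses section is generic and does not expressly assign a test to the primary outcome. That would answer a complaint about silence. Here, however, the text names specific tests, and they conflict with the article's own sample size. Nor can they be read as tests on centre summaries, because a chi-square or Fisher test of a yes/no event needs patient counts.

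Several narrower points do stand:

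- The 17% belongs to the uncorrected chi-square test. Fisher's test or a continuity correction gives about 13% to 14%, and the sample size itself reproduces only with the correction.
- The ICC is back-calculated. If the design effect of 2 refers to the 55 enrolled per centre and 20% are lost, the error is 14.4%. If all 440 are analysed after multiple imputation, it is 16.6%.
- A design effect of 2 may be cautious. At 1.2 the error would be 7.4%.
- The article ties its design effect to the bleeding rate. For the secondary outcomes the direction is known but the size is not. Time in therapeutic range concerns warfarin users only, so it has fewer patients per centre and, at equal ICC, a smaller design effect.
- Centre is not wholly absent, since it is listed as a subgroup factor. That does not correct the variance of the arm comparison. Each centre lies wholly in one arm, so there is not even a within-centre comparison of arms to make.

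These points change the exact size. They do not remove the contradiction.

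**Conclusion.** The concern holds: the analysis as written is wrong for the design, and it must be changed before the data are analysed. Under the article's own design effect of 2, the nominal 5% test of any bleeding has a true error of 16.6% by chi-square, or about 13% to 14% with Fisher's test or a continuity correction. The figure rests on the planning value of 2 and on centres of equal size. Over assumed design effects from 1.2 to 3 it runs from 7.4% to 25.8% and is always above 5%. For secondary outcomes the error is also above nominal wherever outcomes cluster by centre, by an amount that depends on each outcome's own ICC.

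**What to change.** In the Statistical analyses section, replace the patient-level tests for arm comparisons with a method that respects the randomised unit. Two choices would do for the primary outcome:

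- compare the eight centre-level bleeding proportions with a t-test on 6 degrees of freedom; or
- fit a mixed logistic model with a random centre effect and a small-sample degrees-of-freedom correction.

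With four centres per arm the small-sample correction is essential. Choose one method as primary now, before results are known. Use the matching approach for the secondary outcomes, include centre in the multiple-imputation model, and report the estimated ICC with the results. The choice between t and Mann-Whitney tests on patient-level data by a normality test then no longer applies to arm comparisons.

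The change needs no new patients, visits or data, only wording and a few lines of code. P-values and intervals will be less favourable but valid. The sponsor should state the power alongside it: at a design effect of 2, the 6-df test has about 73% power if 20% are lost, below the planned 80%, and about 82% if all 440 are analysed.

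### Multiple imputation is paired with bare chi-square/Fisher and t/Mann-Whitney tests, so the article fixes no single primary p-value; one pooled centre-level estimate would supply it

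*Protocol article*

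**What the plan says.** All the statements are in the Protocol article.

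- **Missing data** (Statistical analyses): "Multiple imputations will be used to fill in missing values".
- **Binary outcomes** (same section): "comparisons between the groups will be performed using the chi-square or Fisher’s exact tests". Any bleeding, the primary outcome, falls here.
- **Continuous outcomes** (same section): a Kolmogorov–Smirnov "test will be utilized to determine the normality of the data", after which a t-test or Mann–Whitney test "will be applied to compare two groups, depending on the distribution of the data".
- **Analysis sets and software** (same section): "both per-protocol (PP) analysis and intention-to-treat (ITT) analysis will be conducted", and "All statistical analyses will be conducted with the IBM SPSS version 22.0 software". Significance is p below 0.05.
- **Expected loss** (Sample size): the calculation is made "with a 20% loss to follow-up rate", and a design effect of 2 brings the total to 440.

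The section names no risk difference, odds ratio, mean difference or model as the quantity to be reported. It does not say which variables are imputed.

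**The concern.** Multiple imputation yields several completed data sets. Rubin's rules turn them into one result by combining an estimate and its standard error from each. Fisher's exact test and the Mann–Whitney test provide neither. A chi-square statistic can be pooled, but only by a special rule. For the scales, a normality screen run in each imputed set could select a t-test in one and a rank test in another, which leaves no common quantity to combine.

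Taken literally, the plan gives the 0.05 threshold several p-values to act on. The Randomization and blinding section says that data analysts are not blinded, so any choice among those p-values would be made with allocation known.

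The named tests also treat patients as independent although centres are randomised. A remedy that only adds pooling would leave that error in place.

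**Working it through.** **Inputs from the article.** Control bleeding 20%, reduction 15%, two-sided 5%, power 80%, loss 20%, design effect 2, total 440, 8 centres, 1:1 allocation.

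**Assumptions.** Four centres per arm with 440/8 = 55 patients each. Bleeding status wholly unknown for the lost 20%, completely at random. m = 5 imputed sets unless stated.

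**1. The plan's own figure.** Reading the reduction as 20% versus 5%:

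- n0 = [1.96·√(2·0.125·0.875) + 0.842·√(0.20·0.80 + 0.05·0.95)]² / 0.15² = 75.1, or 76 rounded up.
- With continuity correction: (75.1/4)·[1 + √(1 + 4/(75.1·0.15))]² = 88.
- 88/0.8 = 110, and 110 × 2 arms × 2 = 440. The figure is reproduced and this point does not affect it.

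**2. One imputed set, no effect, no clustering.** Let V be the variance of the risk difference with all 220 per arm observed. With 80% observed, the observed difference has variance V/0.8 = 1.25V. In one imputed set the difference is 0.8 × observed + 0.2 × imputed. Imputation adds 0.2²·(V/0.8 + V/0.2) = 0.25V, giving 1.50V in all. The chi-square test assumes V, so its error rate is 2·[1 − Φ(1.96/√1.50)] = 2·[1 − Φ(1.600)] = 0.110. Two simulations gave 0.110 and 0.105. Over 5% to 30% missing, the simulated rate runs from 0.068 to 0.150.

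**3. Pooled, no clustering.** Rubin's rules use T = W + (1 + 1/m)·B, where W is the mean within-set variance and B the variance between sets. The reference is t with (m − 1)(1 + 1/r)² degrees of freedom, where r = (1 + 1/m)·B/W. Simulated error rates at 20% missing:

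| Rule | False positives |
|---|---|
| One imputed set | 0.105 |
| Median p over sets | 0.087 |
| All sets below 0.05 | 0.031 |
| Risk difference pooled by Rubin's rules | 0.052 |
| Chi-square pooled by the D2 rule | 0.049 |

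A valid single p-value is therefore available from the same 2×2 table once a pooling route is named.

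**4. Pooled, with the plan's clustering.** 1 + (55 − 1)·ICC = 2 gives ICC = 1/54 = 0.0185. With about 44 observed per centre, the variance is inflated by 1 + 43/54 = 1.80. A patient-level test then has error 2·[1 − Φ(1.96/√1.80)] = 0.144. Simulation gave 0.146 (Rubin), 0.137 (D2) and 0.149 (complete-case chi-square). Pooling does not cure this.

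**5. Centre-level estimate, pooled.** In each imputed set take d = mean of the four centre proportions in one arm minus the mean of the four in the other. Its variance is s1²/4 + s2²/4, where s1² and s2² are the between-centre variances. Pool by Rubin's rules and refer to t on 8 − 2 = 6 degrees of freedom. At ICC 1/54 this gave about 2–5% false positives and about 72–85% power at 20% versus 5%. The patient-level test gave 97%. A repeat with m = 20 and 5,000 trials per cell gave 2.2% and 70% when imputing centre by centre, and 4.7% and 85% when imputing by arm only. The choice of imputation model therefore accounts for the range.

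**The case against.** The strongest reply is that little is wrong beyond an unnamed pooling rule. That rule, the number of imputations and the imputation model are commonly left to the analysis plan, which is not shown. This stands: their absence is no finding. What remains is the choice of tests that the article does state. An analysis plan that kept to those tests alone would inherit the mismatch for Fisher and Mann–Whitney, and would have to add an estimate to resolve it.

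A reader might draw four stronger conclusions that the document does not support:

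- **That no valid primary p-value exists.** Step 3 shows two ways to get one.
- **That the plan runs at 11%.** The article nowhere proposes reading one imputed set. The figure describes a misuse that the wording does not exclude. The same applies to stacking the sets as if they were extra patients, which gives about 44%.
- **That Mann–Whitney and the normality screen damage the primary comparison.** Bleeding is binary, so they affect only scale-type outcomes, and the t-test's mean difference can be pooled directly.
- **That 20% of bleeding outcomes will be imputed.** The article does not say that bleeding is imputed. Outcomes are collected at six visits, so a bleed before dropout is already known, and control patients may be followed by telephone.

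At the planned 20% versus 5%, imputed sets fall on opposite sides of 0.05 in only 2–3% of simulated trials. It is also fair to say that the clustering error is the larger one, and that a cluster-level estimate adopted for that reason would supply something to pool.

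**Conclusion.** The point holds in limited form. The stated analysis joins multiple imputation to tests without a named poolable estimate, so it fixes no single primary p-value, although one is obtainable. With bleeding imputed for up to 20% of patients and no clustering, the error rate is about 11% if one set is read and about 5% if the sets are pooled. At the plan's design effect of 2, a pooled patient-level test still runs at about 14–15%.

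These sizes rest on outcomes missing completely at random, on 20% as an upper-end level of missingness, on four centres per arm and on ICC 1/54. The article gives only the 20% loss, the eight centres, the 1:1 allocation and the design effect. The change should be made because it is cheap and settles both the pooling and the clustering of the primary test.

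**What to change.** **Bleeding and the other binary outcomes.** State one primary analysis: in each imputed set, the difference between arms in mean centre proportions with its standard error, pooled by Rubin's rules with at most 6 degrees of freedom. Include centre and arm in the imputation model. Report one risk difference, 95% CI and p-value.

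**Scale outcomes.** Replace the test chosen by the normality screen with one pre-named cluster-adjusted mean difference. Whether these outcomes are imputed or analysed by a model on observed data is a matter of preference.

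**Chi-square, Fisher and Mann–Whitney.** Keep them as descriptive only. Also say which variables are imputed.

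**Cost.** A few sentences and modest programming. The test is somewhat conservative, at about 2–5% false positives. Power at 20% versus 5% falls to about 72–85%, against 97% for the patient-level test, but that 97% comes from a test whose real error rate is about 14–15%. Imputing separately within each centre sits at the lower end of the power range, so the imputation model should be fixed before data are seen.
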